### Aims and endpoints

The overarching aim of this study is to deepen our understanding of chronic visceral pain by identifying and evaluating the genetic, molecular, and physiological mechanisms that contribute to this condition. We will examine these mechanisms across different participant groups, including those with extreme visceral pain, those with a lack of expected pain despite visceral disease, and healthy controls.

Our **primary objective** is to look for physiological markers (such as changes in movement, heart rate, and postural patterns) that predict or associate with visceral pain flares by examining data from wearable sensors. This will provide objective, real-time insights into how visceral pain affects day-to-day activities, and will be tested using a pre-specified statistical model and is central to the confirmatory aspect of the study.

In addition, we will undertake a series of **secondary/exploratory objectives**, which include the following key areas of investigation:

1**Genetic insights:** We aim to identify and characterize the genetic factors that underlie chronic visceral pain in specific participant cohorts, which include individuals with conditions like polycystic kidney disease, inflammatory bowel disease, chronic pancreatitis, endometriosis, and painful bladder syndrome.2**Spatial and temporal pain mapping:** We will create detailed maps of where and when individuals experience visceral pain. This includes analysing the frequency and intensity of pain reported by participants using a remote mobile app and wearable sensors that track body movement, posture, heart rate, and breathing.3**Biological sample analysis:** We will collect a variety of biological samples—blood, urine, low vaginal swabs, and faeces—from participants to explore pain mediators and modulators. This will include testing human serum in passive transfer experiments using mice to better understand the role of autoantibodies and other pain-related factors [19].4**Comparing pain groups:** We will compare participants with high levels of visceral pain, regardless of disease activity, to those with little or no visceral pain despite having active disease. These groups will be contrasted with healthy control subjects to uncover key differences in pain experience and physiology.

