### Wearable sensors

Participants from Extreme Visceral Pain and Healthy Controls cohorts will use two types of wearable sensors to monitor physiological data:

**Chest *wearable sensor*:** The Discovery *ANNE* Chest System is a flexible, rechargeable sensor worn on the upper chest for up to 16 hours daily over 30 days. It tracks heart rate, respiratory rate, skin temperature, and activity level. Participants will answer two questions daily via a mobile app in a tablet linked to the sensor: “Have you had a visceral pain flare today?” and “Have you changed or cancelled an activity due to visceral pain today?”. To encourage adherence to the wearable sensor usage protocol, instructional videos on how to wear the devices were made publicly available and shared with participants (see Supplementary Information). Additionally, Fig 3 is printed and shared with the participants to provide a visual guide with key steps for sensor setup, syncing, and daily use.

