**Fig 3 pone.0350169.g003:**
[figure not shown]
Wearable Sensor Deployment and Participant Instructions for the ADVANTAGE Study. Chest-worn respiratory sensor and wrist-worn physiological monitor setup for 4-week continuous data collection from Extreme Visceral Pain and Healthy Controls cohorts. Diagram illustrates wireless charging station, 2-metre Discovery App tablet sync range for data upload, daily reapplication protocol (shower before reattachment, correct orientation), and smartphone app for *ad libitum* pain reporting (0-10 Likert scale). Key operational constraints shown: non-waterproof (daily removal for showering), medical imaging contraindication (X-ray/MRI interference), QR code access to instructional videos. Ensures compliance for primary endpoint analysis correlating respiration rate, HRV, activity, and posture against real-time pain scores.

**Upper limb *smartwatch*:** The wrist-worn device (ActiGraph GT9X Link or GENEActiv, for Cambridge and Edinburgh sites, respectively) records limb movement and position continuously for up to 90 days. Data is downloaded after the wearable is returned, either by post or during a follow-up visit.

***ADVANTAGE Diary* remote mobile app questions during wearable sub-study:** Pain severity will continue to be recorded through the *ADVANTAGE Diary* app using the same 11-point scale as with the cohort classification stage. Participants will also receive daily reminders, and those who report pain will be asked additional questions: “How worried are you about that pain?” (rated 0–10), and “What is the position of your body right now?” (options include sitting, standing, lying down, squatting, moving actively). Those using the smartwatch and the *ADVANTAGE Diary* remote mobile app will be invited to continue for up to 90 days or until the smartwatch battery runs out after the follow up visit.

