### Primary endpoint analysis

The primary hypothesis we will test is that specific physiological parameters measured by wearable sensors (such as heart rate, physical activity, or respiration) will associate with self-reported pain intensity and specific body postures, such as sitting or lying down. We hypothesize that:

Higher pain scores will associate with reduced mobility and specific postures (e.g., sitting or lying down).Wearable sensor data will provide objective measures that can predict or associate with self-reported pain intensity.

This hypothesis will be tested using a linear multiple regression model with the following four predictors:

1Heart Rate Variability2Physical Activity (as measured by accelerometery)3Posture (sitting, standing, lying down)4Mean daily respiration rate

We expect that a sample size of n = 100 exclusively for the wearable sub-study provides 80% power to detect a moderate effect size (f² = 0.12 or larger) at p < 0.05, assuming four predictors.

For the primary analysis, we will fit a multiple linear regression model with mean daily visceral pain intensity as the dependent variable and the four pre-specified wearable predictors as independent variables. Model diagnostics will include inspection of residual-versus-fitted plots, Q–Q plots, and tests to assess both normality of residuals and multicollinearity between predictors. If substantial non-linearity or heteroscedasticity is detected, we will explore appropriate transformations of predictors or outcome while retaining the same pre-specified predictor set. All analyses will be conducted using validated statistical packages (either in R or Python), and the final model specification, diagnostics, and code will be documented to support reproducibility.

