These four predictors were selected *a priori* based on established physiological relationships with pain states. Heart rate variability reflects autonomic nervous system engagement known to correlate with pain perception and flare severity in visceral pain syndromes [33–35]. Physical activity reduction is an established behavioural marker of pain avoidance and flare severity [36–38]. Posture is critical in visceral pain as many patients adopt characteristic positions during flares (e.g., lying down during endometriosis flares) [39,40]. Respiration rate was selected over alternative markers (such as skin temperature or sleep metrics) because: (i) it is directly modulated by nociceptive signalling through brainstem-vagal pathways critical to visceral pain processing [41,42], (ii) respiratory patterns are objectively measured with high fidelity by our chest-worn sensors, (iii) respiration is feasible for continuous long-term monitoring without imposing additional participant burden. Skin temperature was not selected due to confounding by environmental factors, and sleep metrics, whilst potentially informative, require longer data epochs incompatible with our primary real-time flare detection objective. No additional predictors will be included in this primary model.

We will use the correlation coefficients and regression analyses described to evaluate associations between these parameters and self-reported pain intensity, measured on an 11-point Likert scale (0–10). Confounding variables such as age, diagnosis, and occupation will not be included in the primary model but will be explored in sensitivity analyses.

Where multiple days of valid wearable data are available per participant, we will first derive participant-level mean values for each predictor over the observation period and use these aggregated values in the primary regression model; this avoids inflating the effective sample size and simplifies interpretation at the participant level. Day-level models will also be explored by using linear mixed-effects models with a random intercept for participant data.

Given that not all participants from the Extreme Pain cohort will use the wearables, the total number of participants we aim to recruit in the Extreme Pain cohort needs to exceed 100 to ensure adequate statistical power for this primary hypothesis. Healthy controls are not included in this confirmatory analysis, as they are unlikely to report sufficient pain scores for reliable modelling.

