Missing data will be addressed using a complete-case analysis approach. No imputation methods will be applied for the wearable sensor data. Analyses will be restricted to participants with valid data for all variables included in the respective models. The extent and pattern of missingness will be reported descriptively. Where appropriate, we will perform sensitivity analyses to assess whether the exclusion of participants with missing data materially affects the results. For transparency, we will report the number of participants and observations included and excluded from each primary and sensitivity model in a CONSORT-style flow diagram and accompanying table. We will also present summary characteristics of participants with and without complete wearable data to allow readers to assess potential selection bias. This approach is justified by the observational nature of the study and the focus on real-world feasibility and data integrity.

This pre-specified analysis aligns with the SPIRIT recommendations for defining and justifying primary hypothesis-testing outcomes in clinical research protocols. All other objectives in this study, including genetic, immunological, and clustering analyses, are exploratory and will be pursued as hypothesis-generating efforts as more data becomes available.

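### Minor: the exploratory day-level model names a random intercept for participant, so its standard errors can be too small if days are serially correlated or slopes differ between people

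*Protocol article*

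**What the plan says.** The confirmatory model in the Primary endpoint analysis section uses a single row for each person: "we will first derive participant-level mean values for each predictor over the observation period and use these aggregated values in the primary regression model". The stated reason is that "this avoids inflating the effective sample size and simplifies interpretation at the participant level". The power statement belongs to that model: n = 100 "provides 80% power to detect a moderate effect size (f² = 0.12 or larger) at p < 0.05, assuming four predictors".

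Daily data enter only as a supplement: "Day-level models will also be explored by using linear mixed-effects models with a random intercept for participant data". The article names no random slope, no residual correlation structure and no robust standard error for this model. The diagnostics it lists (residual and Q-Q plots, checks of normality and multicollinearity) are given for the primary model, and none is aimed at serial dependence.

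The follow-up is long enough for within-person structure to matter. The chest sensor is "worn on the upper chest for up to 16 hours daily over 30 days" and the wrist device "records limb movement and position continuously for up to 90 days" (both under Wearable sensors). The primary objective under Aims and endpoints is to find markers "that predict or associate with visceral pain flares by examining data from wearable sensors".

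**The concern.** The random intercept absorbs a person's overall level of pain. It does not absorb the resemblance of neighbouring days beyond that level, or differences between people in how pain moves with a sensor value. Both are plausible here. The Introduction describes pain that comes in episodes, the cohort mixes several diseases, and the rationale for posture gives an example tied to one of them.

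This is also the only stated model that uses day-to-day variation, which is where flares would show. A regression on participant means cannot tell whether sensor and pain move together within a person. If the day-level standard errors are too small, nominal p-values and intervals from this analysis will overstate the evidence on the flare question. In addition, an undivided daily predictor yields one coefficient that blends the between-person and within-person associations.

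**Working it through.** **The plan's own figure.** The only figure stated is 80% power for the participant-level regression. The overall F test with 4 and 95 degrees of freedom and noncentrality 0.12 × 100 = 12 gives 77.97%; 80% needs n = 105, or f² of about 0.125 at n = 100. That small gap is a separate matter and does not bear on this point. The document gives no error rate for the day-level model, so there is nothing to reproduce there.

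**Inputs.** From the document: 100 participants, about 30 chest-sensor days, up to 90 wrist-device days, two-sided 5%. Assumed: 14 days as a low-adherence case; lag-1 autocorrelation 0 to 0.7; slope SD 0 to 0.3 residual SDs per total SD of the predictor; intraclass correlation (ICC) 0.5 for predictor and outcome; one predictor; true mean slope zero.

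**Approximation.** With autocorrelation r_x in the predictor and r_e in the residual, T days, slope SD s and within-person share w of the predictor's variance, the true variance of the slope estimate exceeds the model-based one by about

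k = (1 + r_x·r_e)/(1 − r_x·r_e) + T·s²·w,

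and type I error is about 2·Φ(−1.96/√k). If r_x or r_e is zero, the first term is 1. Serial correlation therefore does harm only when both predictor and residual have it.

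- r = 0.5 in both, s = 0: k = 1.25/0.75 = 1.667; 1.96/1.291 = 1.518; error 12.9%.
- r = 0, s = 0.2, T = 28, w = 0.5: k = 1 + 28 × 0.04 × 0.5 = 1.56; 1.96/1.249 = 1.569; error 11.7%.
- r = 0.5 in both, s = 0.2, T = 28, w = 0.5: k = 1.667 + 0.56 = 2.227; 1.96/1.492 = 1.313; error 18.9%.
- r = 0.5 in both, s = 0.3, T = 90, w = 0.5: k = 1.667 + 4.05 = 5.717; 1.96/2.391 = 0.820; error 41%.

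**Simulation.** A random-intercept model was fitted by REML, 2,000 replicates per setting (Monte Carlo standard error about 0.5 points at 5% and 1.1 points at 40%). The clustered column uses participant-clustered standard errors on the same fit.

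| Days | Autocorrelation (predictor/residual) | Slope SD | Model-based | Clustered |
|---|---|---|---|---|
| 28 | 0/0 | 0 | 4.7% | 4.6% |
| 28 | 0.3/0.3 | 0 | 7.0% | 5.2% |
| 28 | 0.5/0.5 | 0 | 12.4% | 5.4% |
| 28 | 0.7/0.7 | 0 | 22.2% | 6.7% |
| 28 | 0.3/0.3 | 0.2 | 13.0% | 4.4% |
| 28 | 0.5/0.5 | 0.2 | 19.2% | 5.0% |
| 14 | 0.5/0.5 | 0.3 | 18.4% | 5.3% |
| 90 | 0.3/0.3 | 0 | 7.5% | 5.4% |
| 90 | 0.5/0.5 | 0.3 | 39.8% | 4.2% |

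With autocorrelation in only one of the two and no random slopes, the model-based rate at 28 days was 4.8-5.6%. With random slopes alone at 28 days it was 7.6%, 12.2% and 19.1% for slope SD 0.1, 0.2 and 0.3. Over all 28 settings run with clustered errors, the clustered rate lay between 3.8% and 6.7%.

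**Scale of the slope SD.** If the slope SD is expressed per within-person SD of the predictor (w = 1), an SD of 0.2 at 28 days gives k = 2.12 and 17.8% without autocorrelation, and k = 2.787 and 24.0% with 0.5 in both. Any figure must state its scale.

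**Blending of associations.** At 28 days with both ICCs 0.5 and no autocorrelation, per-person information is 27 × 0.5 = 13.5 within and 14.5/(1 + 28) = 0.5 between. The between-person weight is 0.5/14 = 3.6%. With an outcome ICC of 0.2 the between part is 14.5/(1 + 7) = 1.81, and the weight is 1.81/15.31 = 12%.

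**The case against.** The strongest objection is that this model carries no confirmatory weight. It is to be explored alongside the primary test, and the authors aggregated to participant level precisely because they saw the repeated-days problem. This stands, and it is why the point is minor. A reader might infer that the primary p-value, the sample size or the 5% level is compromised. The documents do not support that, because none of these uses daily rows.

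Second, the article does not say that the random intercept is the only structure, and it promises to document the final specification and code. A condensed article may leave covariance and standard-error details to the analysis plan. This stands in part: random slopes and robust errors are not ruled out. But the article did choose to name a structure, and the one it names is open to this problem.

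Third, a reader might take a figure such as 12% or 23% as the error rate of this study. The documents give no autocorrelation, slope variance or ICC, and under mild inputs the rate stays near 5%. Only a conditional range can be defended.

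Fourth, a reader might infer that the coefficient says nothing about within-person change. With about 28 days it is mostly within-person (between-person weight about 4% to 12% under the assumptions above), so the blending is a matter of clean interpretation and not a serious bias by itself.

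Finally, random slopes for four predictors plus autoregressive residuals, with about 100 participants and missing days, may well fail to converge. That argues for a simpler remedy.

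**Conclusion.** The point holds as a minor one on an exploratory analysis. The random-intercept structure named for the day-level model gives standard errors that are too small if pain and sensor values are both serially correlated, or if slopes differ between people. Under the assumed inputs type I error ranges from about 5% to about 40% against a nominal 5%, with about 12% at 28 days and autocorrelation 0.5 in both. The direction rests on general properties of the model; the size rests wholly on assumed correlations, slope SDs and ICCs, and on simulation with one predictor where the plan has four. What is at stake is how nominal p-values and intervals from this supplementary analysis are read. Whether a regression on participant means serves the flare objective is a different question and does not raise the weight of this one.

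**What to change.** In the day-level model, enter each predictor as two terms, the person's mean and the daily deviation from it, and report participant-clustered (robust) standard errors. Clustering corrects the standard errors; the split makes the daily term a within-person association, which clustering alone does not do. The simulation tested clustering with the undivided predictor, not the split itself. Where they converge, random slopes for the daily deviations or first-order autoregressive residuals can be added as a sensitivity analysis.

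The change takes a few lines of code and no new data. The Study status section says that no analysis has been done, so it can still be pre-specified. The downside is somewhat wider intervals.

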### Key exploratory endpoint

The goal at the exploratory phase is to identify genetic variants that regulate visceral pain in people with visceral pain disorders, or in individuals who continue to experience pain despite remission or treatment. While we aim to conduct hypothesis-generating research, the genetic analysis will focus on identifying potential variants with moderate to strong effects, acknowledging that smaller effect sizes may require larger cohorts for reliable detection. The genetic approaches used have been proven effective in cohorts as small as 30–200 individuals with pain phenotypes [18]. However, we acknowledge that the requirement for ≥30 exomes per visceral disease pain phenotype may limit statistical power to detect genetic variants with modest effect sizes. Our analysis will explicitly report effect sizes, confidence intervals, and limitations related to sample size constraints in all genetic findings. Where modest effect sizes are detected, these will be flagged as requiring replication in larger cohorts. Findings will be reported in line with STREGA and STROBE guidelines for genetic association studies.

We note the following:

At least 30 exomes are required per visceral disease pain phenotype to yield statistically valid results, in terms of the power to detect significant associations between genetic variants and pain phenotypes.DNA extraction failure rates are expected to be no more than 5% from blood samples and negligible from serum samples.

For this study, the following visceral pain phenotypes will be analysed, representing a broad spectrum of pain associated with visceral organ pathology:

1Polycystic kidney disease2Inflammatory bowel disease3Post-vaginal mesh surgery4Chronic pancreatitis5Endometriosis6Painful bladder syndrome

Additionally, similar analyses will be conducted in the Lack of Visceral Pain cohort, where the severity of visceral disease does not correspond to expected levels of pain. This group will allow us to explore potential genetic mechanisms underlying discordant pain experiences. The following phenotypes will be included in this cohort:

1Polycystic kidney disease2Inflammatory bowel disease3Chronic pancreatitis4Chronic pain syndromes (e.g., fibromyalgia, Complex Regional Pain Syndrome, migraine)5Cases of painlessness during percutaneous visceral organ procedures (e.g., biopsies)6Overactive bladder syndrome

This group will provide an exploratory dataset to investigate genetic variants that may regulate pain perception independent of disease severity.

**Mendelian gene effects** will be explored through multiple exome analyses, conducted in three steps:

1Candidate genes2Genes identified in ADVANTAGE pre-clinical research as important for visceral pain in rodents3Agnostic analysis to discover unknown genes associated with visceral pain

These methods, widely used in UK Clinical and Medical Genetics practice, will compare results to local, national, and international normative databases.

**Functional SNP allele discovery (fSNPd)** will be used to detect Single Nucleotide Polymorphisms (SNPs) that may cause a pain phenotype triggered by environmental factors [43]. The approach is based on three principles:

SNP alleles that cause fully penetrant effects are likely to be exonic and protein-changing (e.g., mis-sense, non-sense, indels, or splicing).Exome sequencing can detect most of these SNPs.Smaller cohorts are easier to collect, phenotype, and examine.

We will analyse exomes from multiple individuals to identify SNPs that occur at significantly different frequencies compared to the general population. Confounding variables will be minimized by matching subsets of control cohorts based on ethnicity or country. SNPs with significantly higher or lower allele frequencies in the study population will be identified through a two-tailed chi-squared test with Bonferroni and false discovery rate corrections applied.

Exome data will also be analysed for **mitochondrial genome variants** using methods developed in [name] laboratory at the MRC Mitochondrial Biology Unit. Any findings are expected to be mosaic. These results will be compared to established normative ranges for human mitochondrial variants.

Mitochondrial variants will be evaluated for **heteroplasmy levels** and potential **mosaic/somatic variants** using established bioinformatics pipelines and clinical reporting thresholds appropriate for the specific analysis platform and cohort characteristics. Variant calling and heteroplasmy quantification will follow current best practices as defined by relevant clinical genomics standards and validated reference databases. All mitochondrial variant findings will be interpreted in the context of established population frequency data and clinical significance guidelines current at the time of analysis.

All exome and mitochondrial analyses will be performed using established, version-controlled bioinformatics pipelines, and we will document the exact software versions, parameter settings, and reference genomes used in a methods appendix or subsequent data descriptor.

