### Bio-sampling

Participants from Extreme Visceral Pain and Lack of Visceral Pain cohorts will be asked to provide various samples to help researchers understand the similarities and differences in how conditions affect chronic visceral pain. Participants may choose to donate some samples while opting out of others, including those used in research involving non-human models.

**Whole blood:** Up to 50 mL of whole blood will be obtained through venepuncture. 5 mL of the whole blood sample will be sent for DNA extraction at the Department of Medical Genetics, University of Cambridge. 40 mL of the whole blood sample will be processed and sent for analysis and long-term storage to the Wolfson Sensory, Pain and Regeneration Centre at King’s College London. 5 mL of the whole blood sample will be processed and sent for long term storage to the Centre for Reproductive Health, Institute for Regeneration and Repair, University of Edinburgh.

**Urine:** Participants will collect mid-stream urine samples using a sterile device (UNI0054 or Colli-pee) at home or in the clinic, returning the samples via post. The urine sample will be sent to the Centre for Reproductive Health, Institute for Regeneration and Repair, University of Edinburgh.

**Vaginal swab:** Participants will self-collect a low vaginal swab (using BBLtm culture Swab MaxV or OMNIgene•vaginal | OMR-130), following provided instructions, and return the sample by post. The vaginal swab samples will be sent to the Centre for Reproductive Health, Institute for Regeneration and Repair, University of Edinburgh.

**Faeces:** Participants will collect up to three samples (using OMNIgene•GUT | OMR-200) at home and send them by post to the Cambridge Institute for Medical Research, University of Cambridge.

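### The exploratory SNP scan sets study exomes against general-population frequencies and matches only on ethnicity or country, so technical differences between the data sets can appear as associated SNPs

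*Protocol article*

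**What the plan says.** All of this is in the protocol article. The fSNPd paragraph under *Key exploratory endpoint* sets the comparison: "We will analyse exomes from multiple individuals to identify SNPs that occur at significantly different frequencies compared to the general population". On confounding it says: "Confounding variables will be minimized by matching subsets of control cohorts based on ethnicity or country". The test is a "two-tailed chi-squared test with Bonferroni and false discovery rate corrections applied".

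The same section gives one size figure: "At least 30 exomes are required per visceral disease pain phenotype to yield statistically valid results". It supports the approach with the statement "The genetic approaches used have been proven effective in cohorts as small as 30–200 individuals with pain phenotypes".

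On who gives DNA, *Bio-sampling* says: "Participants from Extreme Visceral Pain and Lack of Visceral Pain cohorts will be asked to provide various samples". The assessment list under *Participant recruitment* marks sample collection as not applicable to Healthy Controls. The caption of Figure 1, however, has Healthy Controls going on to a return visit that includes optional bio-sampling.

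Two safeguards are stated. One concerns the pipeline: "All exome and mitochondrial analyses will be performed using established, version-controlled bioinformatics pipelines", with software versions, settings and reference genomes to be documented. The other concerns replication: "Where modest effect sizes are detected, these will be flagged as requiring replication in larger cohorts". *Primary endpoint analysis* labels all genetic work exploratory and hypothesis-generating.

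**The concern.** A frequency comparison is interpretable only if a variant has the same chance of being seen in both data sets. Here the cases are exomes sequenced for the study, and the comparison is with the general population. If the two sources differ in capture kit, depth, caller or site filters, a variant may be called in one and missed or filtered out in the other. The test then rejects because of the method, with no biological difference.

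Ethnicity and country matching addresses ancestry, not technique. Multiplicity correction assumes valid p-values under the null, and a systematic difference breaks that assumption. Version control makes the study's own calls reproducible but says nothing about the reference. The replication flag covers modest effects, whereas a technical artefact at a rare site looks like a large one and would not trigger it. What is at stake is whether the SNPs reported from the scan can be trusted as leads.

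**Working it through.** **The plan's own figure.** The minimum of 30 exomes cannot be reproduced: the article gives no alpha, number of SNPs tested, effect size, reference frequency or power for it. The point does not depend on it.

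**Inputs.** From the article: 30 exomes, hence 2 × 30 = 60 alleles; two-tailed chi-squared test; Bonferroni correction. Assumed, because the article gives no values: family-wise alpha 0.05; 20,000 SNPs tested, so the threshold is 0.05 / 20,000 = 2.5e-6 (chi-squared on 1 df above 22.17); a reference of 100,000 alleles; no true association.

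**Formula.** With a and b the variant and other alleles in the study, c and d the same in the reference, and N the total:

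X² = N(ad − bc)² / [(a+b)(c+d)(a+c)(b+d)]

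The continuity-corrected form replaces |ad − bc| by |ad − bc| − N/2.

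**Reference frequency 0.1%** (c = 100, d = 99,900)
- 1 of 60 alleles: X² = 14.60, p = 1.3e-4. Does not pass.
- 2 of 60 (b = 58): ad − bc = 199,800 − 5,800 = 194,000. X² = 100,060 × 194,000² / (60 × 100,000 × 102 × 99,958) = 61.56, p = 4e-15. Corrected: X² = 33.90, p = 6e-9. Passes.

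**Reference frequency 1%** (c = 1,000, d = 99,000)
- 4 of 60 alleles: X² = 19.38, p = 1.1e-5. Does not pass.
- 5 of 60 (b = 55): ad − bc = 495,000 − 55,000 = 440,000. X² = 100,060 × 440,000² / (60 × 100,000 × 1,005 × 99,055) = 32.43, p = 1.2e-8. Corrected: X² = 25.48, p = 4.5e-7. Passes.

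So two people wrongly called heterozygous at a rare site, or five at a 1% site, would be enough. With 100,000 tests (threshold 5e-7) the same counts still pass.

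**Sensitivity to the test.** Expected counts are only 60 × 0.001 = 0.06 and 60 × 0.01 = 0.6, where the chi-squared approximation is poor, so part of the extremeness comes from the test itself. Exact one-sided binomial tails need more alleles: 4 at 0.1% (p = 4.7e-7), and 7 at 1% (p = 2.4e-6, which fails if doubled to 4.9e-6). The mechanism remains, at higher counts.

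**Chance of passing if a 0.1% site is read at 5% for technical reasons.** Chi-squared: P(X ≥ 2) = 1 − 0.95^60 − 60 × 0.05 × 0.95^59 = 0.81, against 0.0017 without the artefact. Exact tail: P(X ≥ 4) = 0.35, against 4.7e-7. If the site is read at 2%, the figures are 0.34 and 0.03; at 10%, 0.99 and 0.86.

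**Where the effect is weak.** Under-calling a common allele matters little at 30 exomes: 30% read as 15% passes with probability 0.0007. At 100 and 200 exomes the probability is 0.47 and 0.99, so for distortions of this size a larger cohort increases the problem.

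**The case against.** The strongest reply is that this is a condensed article. Call-level quality control (callable regions, depth limits, joint calling) is often left to a fuller document. fSNPd is a cited method whose source is not at hand, and nothing says that the reference will be used unfiltered. That stands as a limit: silence on a filter is not evidence that there is none. The point therefore rests on what the article does fix: the comparator, the matching variables offered as the control of confounding, and the absence of study-sequenced controls for this test.

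Several stronger readings are tempting, and the documents do not support them.
- A reader might infer that case status is completely confounded with sequencing platform. The article does not say whether its control cohorts are individual exomes or published frequencies, or who sequenced them. Local databases are mentioned, though for the Mendelian analysis. The Figure 1 caption also leaves it unclear whether Healthy Controls are ever sampled.
- A reader might infer that hits go straight into functional experiments. No section says so; the mouse work described uses serum and antibodies.
- A reader might infer a number of false hits, or that artefacts would make up most of the list. Either needs a rate of discordant sites, which the article does not give.

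It is also fair to say that the genetic work is exploratory, and that effect sizes, confidence intervals and STREGA/STROBE reporting are promised. Exploratory status excuses low power and lack of confirmation. It does not protect against a systematic difference between data sources, and confidence intervals do not reveal one.

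**Conclusion.** The point holds as a bias left open by the stated comparison, of moderate weight because the scan is exploratory and no primary conclusion depends on it. As written, the only control of confounding addresses ancestry, and none of the stated safeguards addresses technical comparability with the reference.

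The illustrative counts, 2 of 60 alleles at 0.1% and 5 of 60 at 1%, show how little discordance the stated test needs. They depend on the assumed 30 exomes, reference size and number of tests. They are not an estimate of false hits in this study, which the documents do not allow.

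**What to change.** Add to the fSNPd paragraph, or to the document that governs it:
- Test only sites that are adequately covered and pass filters in both study and reference data.
- Where raw data for control exomes are already available, re-call them with the study pipeline and use them as the comparator.
- Run the same test on synonymous SNPs as a negative control, and treat hits as uninterpretable if that set is inflated.
- Inspect the reads behind each hit before reporting it.

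Also reconcile the optional bio-sampling in the Figure 1 caption with the statement that sample collection does not apply to Healthy Controls, and state whether any such samples have a role in this test.

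The cost is bioinformatics time and the loss of some sites from testing. No new samples or assays are needed, and the primary endpoint is untouched. *Study status* says that no data analysis has been performed, so the rules can still be set before results are seen.
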